#### Total active range of motion

Total active range of motion of the injured fingers and of the corresponding contralateral fingers will be measured with a goniometer for small joints (Fabrication Enterprises, White Plains, NY, USA). Participants will sit in front of the rater, elbow on a table, palm of the hand upturned. The arms of the goniometer will be laid along extension side. The total active range of motion is calculated by summation of the range of motions for flexion and extension of all joints of the concerned finger. The total active range of motion will be a secondary endpoint.

#### Pain, cold intolerance, and hypersensitivity

Individuals will be asked to self-report pain, cold intolerance and hypersensitivity experienced in the last week on a 100-mm visual analog scale, ranging from 0 (no symptoms) up to 10 (maximum of symptoms) by drawing a point. Visual analog scales are well validated for the measurement of acute and chronic pain [23]. Pain, cold intolerance, and hypersensitivity will be secondary endpoints.

#### Appearance of neuroma

The existence of a neuroma will be assessed by local percussion of the injured nerve site. Electrifying pain will be valued as suspicious for a neuroma. These findings will be verified by neurosonography (linear device, 14 MHz frequency). A final data report will include the count of clinical suspicious neuroma and the count of verified neuroma by sonography. The appearance of neuroma will be a secondary endpoint.

Table 1 summarizes study outcome measures.

**Table 1 Tab1:** Study outcome measures

Item	Outcome measurement [unit]	Time point of measurement	Primary/secondary outcome parameter?
Tactile gnosis**	Static 2-point-discrimination [mm]	at 6 months postoperatively**	primary**
Tactile gnosis**	Static 2-point-discrimination [mm]	at 3, 12, and 24 months postoperatively**	secondary**
Sensory re-innervation	Semmes Weinstein method [grading]	at 3, 6, 12, and 24 months postoperatively	secondary
Disabilities in activities of daily living	DASH questionnaire [score]	at 3, 6, 12, and 24 months postoperatively	secondary
Grip strength	Jamar dynamometer [kg; percentage of contralateral side]	at 3, 6, 12, and 24 months postoperatively	secondary
Motion	Total active range of motion [degree]	at 3, 6, 12, and 24 months postoperatively	secondary
Pain, cold intolerance, hypersensitivity	Visual analog scales [points out of ten]	at 3, 6, 12, and 24 months postoperatively	secondary
Appearance of neuroma	Clinical examination and sonography [count]	at 3, 6, 12, and 24 months postoperatively	secondary

** Tactile gnosis measured by static two-point-discrimination 6 months postoperatively will be considered as the primary outcome parameter. Tactile gnosis** measured by the static two-point discrimination at 3, 12, and 24 months postoperatively will be considered as the secondary outcome parameters

In addition, adverse events (any type of revision surgery, incidence of postoperative hematoma, deep wound infections, disturbances of scar formation such as hypertrophic or instable scars) will be recorded during the hospital stay (approximately 5 days) and retrospectively in the follow-ups. Revision surgery of one affected site will be considered as an adverse event even in cases of multiple nerve injuries. Furthermore, the number of pre- and post-randomization dropouts will be registered and analyzed in a descriptive statistic.

### Sample size/power calculation

Assumptions for the primary outcome parameter of the standard treatment can be made from the literature [2, 14] and from our own patients. The mean of 2-PD after 6 months is approximately 8 mm with a standard deviation of 3 mm. A decrease of 2 mm in the 2-PD would be clinically relevant [16] and is assumed for the experimental intervention. Using a two-sided *t*-test with a level of 0.05 and a power of 80 %, 37 individuals per group will be required in order to show superiority. In order to compensate for loss to follow-up, 50 individuals per group will be randomized.

Before implementing the trial design, we analyzed the computerized medical records of our patients retrospectively, to determine how many individuals would have fit our scheme of inclusion and non-inclusion criteria per year. We discovered that we could have included at least 50 individuals per year in the last 3 years. With respect to the unequal number of hand surgical cases in the three centers, the intention is to enroll 100 individuals per year: 50 individuals in the BG Trauma Center Ludwigshafen, 25 individuals in the BG Trauma Center Frankfurt am Main, and 25 individuals in the BG Trauma Center Bochum. The study is intended to take place over a period of 36 months: 12 months for recruitment of all individuals, 18 months from the beginning of the trial for completion of the primary outcome parameter, and 36 months from the beginning of the trial to the completion of all follow-ups.

### Statistical analysis

The primary endpoint will be tested in the per-protocol set via an analysis of covariance with center as factor and distance between lesion and finger pulp as covariate. The test in the full analysis set is to be considered as the sensitivity analysis. Secondary endpoints will be described statistically without confirmatory analysis. Adverse events will be listed with detailed information concerning sort, timing, severity, and mandatory countermeasures.

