## Methods/Design

### Design of the study and setting

To answer the question of whether the additional use of a chitosan nerve tube in primary microsurgical repair of traumatic sensory nerve lesions of the hand without a gap will improve the recovery of sensitivity, a randomized controlled multicenter trial with parallel group design was planned to show superiority for the additional use of a nerve tube. This study will enroll participants with traumatic sensory nerve lesions from three Centers: the BG Trauma Center Ludwigshafen (Ludwigshafen, Germany), BG Trauma Center Frankfurt am Main (Frankfurt am Main, Germany), and BG Bergmannsheil Bochum (Bochum, Germany). Trauma Center Ludwigshafen will be the executive study center.

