### Outcomes

The primary study objective is the recovery of sensitivity. The assessment will follow the guidelines developed by Rosén [19]. Recovery of sensibility will be assessed by static two-point discrimination (tactile gnosis) and the Semmes Weinstein method (sensory re-innervation). The static two-point discrimination (2PD) after 6 months will be the primary outcome parameter. The 2PD does characterize the sensory capability of the injured finger and is a standard method used in the past for clinical assessment of a variety of artificial nerve tubes [14]. The distance between the lesion and the finger pulp will be attributed in the statistical analysis.

Sensory re-innervation, DASH-score, grip strength, total active range of motion, pain, cold intolerance and hypersensitivity, and the appearance of neuroma will be secondary outcome parameters.

All outcome parameters are frequently used in hand surgery research.

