#### Experimental group

Participants who are allocated to the experimental group will be treated with an additional chitosan nerve tube. The injured nerve will be exposed and neurolysed for a distance of 2 cm on each side of the lesion. From this point forward, a microscope will be used. The injured ends of the nerve will be sparingly freshened. The chitosan implant will be pre-soaked for 10 minutes in saline. Afterward, the implant (with a length of 1 cm and an inner diameter of 2.1 mm) will be imposed on the proximal nerve stump. A complete tension-free epineural coaptation of the nerve ends will follow, using several 9–0 USP (United States Pharmacopoeia-System) nylon micro-sutures (German Sutures SAS, La Barbiniere, Beaurepaire, France).

Finally, the nerve tube will be positioned at the site of the suture and fixed to the epineurium with a single stitch on each side using a 9–0 USP (United States Pharmacopoeia-System) nylon micro-suture. The use of the chitosan-based nerve tube is already an authorized and CE-certified German medical product (Reaxon® Nerve Guide, Medovent, Mainz, Rheinland-Pfalz,  Germany)

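### The only confirmatory test of a superiority trial is run in the per-protocol set, so exclusions after allocation can bias it by an unknown amount in either direction

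*Protocol article*

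**What the plan says.** Under Design of the study and setting, the protocol article says the trial "was planned to show superiority for the additional use of a nerve tube". The Hypotheses section is framed the same way: the null is that the tube is equal or inferior. The Outcomes section fixes the endpoint: "The static two-point discrimination (2PD) after 6 months will be the primary outcome parameter".

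Statistical analysis then states: "The primary endpoint will be tested in the per-protocol set via an analysis of covariance with center as factor", with the distance from lesion to finger pulp as covariate. The next sentence reads: "The test in the full analysis set is to be considered as the sensitivity analysis". The same section excludes secondary endpoints from confirmatory testing.

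No reason is given for this order of the two sets, and nothing elsewhere in the article overrides it. The Outcomes section (text after Table 1) says that dropouts after randomization will be described. Sample size/power calculation attributes the increase from 37 to 50 per group to loss to follow-up.

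**The concern.** In a superiority trial, the analysis that keeps participants in their allocated groups is the standard primary analysis, because only that comparison rests on the allocation. A per-protocol set is formed afterwards, by events that may be related both to the treatment given and to how the patient is doing. The article reverses the usual order: the selected subset decides the trial, and the set that preserves the allocation has no deciding role.

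This is a stated choice and not a gap that an analysis plan would fill. A later document could define the sets, but the article has already fixed which of them carries the confirmatory claim. At stake is whether a conclusion that the tube is superior, or a failure to show it, reflects the treatment or the exclusions.

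**Working it through.** **1. The plan's own figure.** Inputs from Sample size/power calculation: SD 3 mm, difference 2 mm, two-sided level 0.05, power 80%. The exact two-sample t-test with standardised difference 2/3 needs 36.31 per group, rounded up to 37. This reproduces the stated 37. Power is 80.8% at 37 per group and 91.0% at 50. Going from 37 to 50 allows for a loss of 1 − 37/50 = 26%. The sample size arithmetic is not at fault.

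**2. How exclusions shift the difference.** Let a fraction q of the tube arm be excluded, and let those excluded have 2PD that is m mm worse than the mean of the whole arm. The mean of those who remain is then better by

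shift = q·m / (1 − q).

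Assumptions, none of them from the article: no true effect, exclusions in the tube arm only, 50 per group before exclusion, SD kept at 3 mm, covariates ignored. The standard error is 3·√(1/50 + 1/(50(1 − q))). The type I error is Φ(shift/SE − 1.96) + Φ(−shift/SE − 1.96).

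For q = 10%, 45 tube participants are compared with 50 controls, and SE = 3·√(1/50 + 1/45) = 0.616 mm.
- m = 0 (exclusions unrelated to prognosis): shift 0, type I error 5%.
- m = 2 mm: shift 0.1 × 2/0.9 = 0.22 mm, type I error 6.5%.
- m = 4 mm: shift 0.1 × 4/0.9 = 0.44 mm, type I error 11.1%.

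Other assumed rates, with m from 2 to 4 mm:

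| Excluded | Shift (mm) | Two-sided type I error |
|---|---|---|
| 5% | 0.11 to 0.21 | 5.3 to 6.4% |
| 10% | 0.22 to 0.44 | 6.5 to 11.1% |
| 20% | 0.50 to 1.00 | 12 to 35% |

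**3. Upper bound at 10%.** If exactly the worst 10% of a normally distributed tube arm are removed, the shift is SD·φ(z)/(1 − q) = 3 × 0.1755/0.9 = 0.58 mm, and the type I error is about 16% at 45 versus 50. Those removed would average 3 × 0.1755/0.1 = 5.3 mm above the arm mean, so this is a limit and not an expectation.

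**4. Opposite direction.** The formula is symmetric. The same selective exclusions in the control arm produce shifts of the same size against the tube.

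**5. Price of the full analysis set.** If a fraction of the tube arm receives no tube and gains nothing, a 2 mm effect is diluted to 2(1 − fraction). With 10% (an assumption) it becomes 1.8 mm:

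| Effect | Power at 50 analysed per group | Power at 37 |
|---|---|---|
| 2.0 mm | 91% | 81% |
| 1.8 mm | 84% | 72% |

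**The case against.** The strongest reply is that the two sets may hardly differ. The treatment is a single operation, participants and follow-up raters are blinded, and the main attrition the article plans for is loss to follow-up, which is not specific to the tube. The full-analysis test is also prespecified, so a discrepancy would be visible. All of this lowers the risk. It does not remove it, because a visible discrepancy would still leave the per-protocol result as the confirmatory one.

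A reader might go further and infer that the bias must favour the tube: only that arm can fail to receive its implant, the Experimental group section gives one size ("the implant (with a length of 1 cm and an inner diameter of 2.1 mm) will be imposed on the proximal nerve stump"), and complications of the tube would take its worst results out of the analysis. The article does not support this. It reports no problem with fit or placement. It records revision surgery as an adverse event and does not say that revision removes anyone from the per-protocol set. Haematoma, infection and revision can occur in either arm, and a control given a tube would also be a deviation.

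Nor can it be concluded that membership of the set will be decided with knowledge of allocation. The Blinding section restricts unblinding to the trial leaders, after dropout or at completion, and the procedure for fixing the set may stand in a document not shown.

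**Conclusion.** The point holds as a wrong choice of primary analysis set. The article makes the per-protocol set decide the sole confirmatory test of a superiority trial, and that test can be biased by exclusions after allocation.

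The direction and size of the bias are unknown. The illustrative range at 10% exclusion in the tube arm starts at no bias, runs to 0.22–0.44 mm (type I error about 6.5–11%) for moderately selective exclusions, and ends at 0.58 mm (about 16%) for the extreme case. These figures rest on assumed exclusion rates, an assumed prognosis of those excluded, and exclusions confined to one arm. They show what the choice permits and do not predict what will happen. The choice should be changed because it governs the trial's only confirmatory claim and the correction is simple.

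**What to change.** In Statistical analysis, exchange the roles of the two sets. The confirmatory ANCOVA, with the same factor and covariate, is run in the full analysis set, with participants analysed as allocated, whatever treatment they received and whether or not they had revision surgery. The per-protocol analysis becomes supportive, with its membership fixed before the allocation is merged with the outcome data.

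The change takes two sentences. Neither the sample size nor surgical eligibility needs to change. The cost is dilution if participants do not receive their allocated treatment. In the 1.8 mm example, power stays above the planned 80% if all 50 per group are analysed, but falls below it if losses leave only 37. The sponsor should accept that cost knowingly. The swap does not address the selection bias at entry that the Discussion concedes for the alternating lists.

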The assessment of sensory recovery after peripheral nerve surgery also remains challenging. Sensitivity of the hand is a complex process and can only be assessed with several tests addressing a variety of partial functions. Strictly speaking, the two-point discrimination (2-PD) is just an assessment tool for tactile gnosis. Tactile gnosis is the ability to recognize shapes and is a marker of functional recovery [15]. An age-related decline was shown in healthy individuals [16]. Based on that fact, nerve regeneration has often been postulated also to decrease with age [17], but this has not yet been proven. More importantly, interfering variables such as the distance from the lesion to the finger pulp exist. This distance was the only interfering variable that was shown in Meeks meta-analysis [14]. However, measuring the two-point discrimination provides a ratio of scaled values, making it particularly suitable for a scientific approach. The Semmes-Weinstein monofilament test, in contrast, assesses the ability for the perception of cutaneous pressure and is a marker for re-innervation in a stricter sense but does result in categories and thereby in a minor level of measurement [18].

The objective of this study protocol is to evaluate whether the additional use of a chitosan nerve tube in the primary microsurgical repair of traumatic sensory nerve lesions of the hand without a gap has an effect on convalescence and functional results.

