### Follow-up

During follow-up, the prepared CRFs will be used by the rater. These CRFs will already include age, gender, profession and current activity, mechanism of the accident, handedness, medical history concerning the hands, date and time of injury, injured side, injured finger, injured nerve, concomitant trauma, and distance from lesion to finger pulp.

Follow-up examinations will be performed after 3, 6, 12, and 24 months. The parameters described below will be measured at 3, 6, 12 and 24 months. Each assessment will take approximately 45 min. In all study centers, medical postgraduates have been employed for the follow-up examination. These raters are explicitly excluded from the screening, randomization, and operative procedure.

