#### Tactile gnosis: static two-point discrimination (2PD)

The ability of perception of either one or two points of touch will be assessed using a compass (NCD Medical/Prestige, Los Angeles, CA, USA). Participants will sit in front of the rater with the dorsum of the hand on the table. Test will be performed on the halves of finger pulps with preoperatively failed nerve-specific receptive fields and on the correlating finger pulps of the contralateral hand. Pressure is defined by self-weight of the compass (10 g). Two points will be applied in a longitudinal direction with decreasing distance between them until they are perceived as one point. Final distance (in mm) will be the final value. The 2PD measured at 6 months will be the primary outcome parameter; the other values measured at 3, 12 or 24 months will be regarded as secondary outcome parameters.

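### The primary ANCOVA omits age, a baseline variable already recorded and linked by the protocol to 2PD; adding it would be a cheap, probably modest gain in precision

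*Protocol article*

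**What the plan says.** The Statistical analysis section of the protocol article fixes the primary model as an "analysis of covariance with center as factor and distance between lesion and finger pulp as covariate", run in the per-protocol set, with the full analysis set as sensitivity analysis.

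Three other places bear on this choice:

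- **Age is available at baseline.** Under Follow-up: "These CRFs will already include age, gender, profession and current activity". The preoperative inclusion criteria (Participants) allow ages 18 to 67.
- **Age is linked to 2PD.** The Background says: "An age-related decline was shown in healthy individuals". It then notes that a decline of nerve regeneration with age has been postulated but not proven. It names lesion-to-pulp distance as the one interfering variable that the cited meta-analysis showed.
- **Contralateral 2PD is measured, but only at follow-up.** The 2PD section has the test done on the affected pulp halves "and on the correlating finger pulps of the contralateral hand". The Follow-up section places these measurements at 3, 6, 12 and 24 months.

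The sample size section assumes for standard treatment: "The mean of 2-PD after 6 months is approximately 8 mm with a standard deviation of 3 mm". It takes a 2 mm improvement as the target difference for the tube. From these it concludes: "Using a two-sided *t*-test with a level of 0.05 and a power of 80 %, 37 individuals per group will be required". No reduction of the SD for covariates is claimed.

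**The concern.** The endpoint is an absolute distance in mm on the injured finger, with no pre-injury value. If normal 2PD worsens with age, a repaired finger in an older patient may read worse than one in a younger patient even when both nerves regenerate equally well. Over a span of almost 50 years that variation would sit in the error term, although a variable known before surgery could remove some of it.

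What is at stake is precision: the width of the confidence interval and a few points of power in a trial planned on about 37 evaluable patients per group. In addition, a chance difference in age between the groups would not be taken out of the estimate.

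**Working it through.** **Inputs.** From Sample size/power calculation: difference 2 mm, SD 3 mm, two-sided alpha 0.05, power 80%, 37 per group needed, 50 per group randomized. From Statistical analysis: treatment, center (three centers, so 2 df) and distance (1 df). Assumed, because the documents do not give it: the additional share R² of outcome variance that age explains, taken as 0%, 5%, 10% and 15%. Also assumed: the 3 mm is the SD left after center and distance.

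**Step 1: reproduce the plan's figure.** Noncentrality = 2 / (3·√(2/n)). For n = 37, the standard error is 3·√(2/37) = 0.697 mm and the noncentrality 2.867. The exact two-sided t-test with 72 df has power 0.808. For n = 36, power is 0.797. So 37 per group is the smallest number that reaches 80%, and the stated figure is correct.

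**Step 2: the planned ANCOVA.** Error df = 74 − 2 − 3 = 69. Power is 0.807, and the half-width of the 95% confidence interval is 1.39 mm.

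**Step 3: add age.** Error df = 68. The residual SD becomes 3·√(1 − R²). Chance imbalance in age raises the variance of the treatment estimate by an expected factor of about 68/67 = 1.015. The standard error is therefore 3·√(1 − R²)·√(2/37 × 1.015).

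| Added R² (assumed) | Residual SD (mm) | Standard error (mm) | Power at 37 per group | 95% CI half-width (mm) |
|---|---|---|---|---|
| planned model | 3.00 | 0.697 | 0.807 | 1.39 |
| 0% | 3.00 | 0.703 | 0.801 | 1.40 |
| 5% | 2.92 | 0.685 | 0.821 | 1.37 |
| 10% | 2.85 | 0.667 | 0.841 | 1.33 |
| 15% | 2.77 | 0.648 | 0.861 | 1.29 |

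The change in power against the planned model is −0.6, +1.4, +3.4 and +5.4 points. Break-even is at an added R² of about 1.5%.

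**Step 4: size of a chance age imbalance.** If ages were uniform over 18 to 67 (assumption), their SD would be 49/√12 = 14.1 years. The 95% range for the difference in group means would be ±1.96 × 14.1 × √(2/37) = ±6.4 years. At the edge of that range the shift in the 2PD difference is 1.96·√(2/37)·3·√R², that is 0.31 mm for R² = 5% and 0.53 mm for R² = 15%, against a target of 2 mm. The age SD cancels, so this shift does not depend on the uniform assumption.

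**The case against.** **The authors did consider age.** The Background calls the age effect on regeneration unproven and says that distance was the only interfering variable found. This explains why distance is in the model. It does not show that age is irrelevant: the caveat is about regeneration, whereas the endpoint is absolute 2PD, for which the same paragraph reports a decline with age. What stands is that a gradient in healthy fingers does not guarantee a useful one six months after repair.

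**The plan is valid as it is.** This stands. Leaving a prognostic variable out of a linear model does not bias a properly randomized comparison, and the standard error already covers chance imbalance. The sample size uses an SD with no covariate reduction.

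**Stronger readings that a reader might infer, and why they fail:**

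- *Contralateral 2PD should also be in the primary model as a stand-in for baseline.* The protocol never says that it predicts 2PD of the injured finger; it only has it measured. The value is taken after randomization, is lost when the visit is missed, may be unusable in bilateral injury, and is not unique when several nerves are injured, which the Interventions section allows. An implant in one hand is unlikely to alter the other, but it is still not a baseline variable. That the article states no use for it in the 2PD analysis is a detail that a condensed article may leave to the full protocol.
- *The adjustment is free.* It is not: if age explains nothing, about 0.6 points of power are lost. With both variables, break-even rises to roughly 3% added R².
- *The omission biases the result because allocation uses alternating lists.* The Discussion concedes a risk of selection bias from that method, but this is a separate weakness. Nothing shows that it acts through age, and adjusting for age would not repair it.

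**Conclusion.** The point holds as a low-cost improvement, not as an error. The primary model leaves out a true baseline variable that is already collected and that the protocol itself relates to 2PD.

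The gain is about 1 to 5 power points for an added R² of 5% to 15%. The half-width of the confidence interval narrows from 1.39 mm to between 1.37 and 1.29 mm. If age explains nothing, the loss is under one point. These figures rest on an R² that the documents do not supply, on 37 evaluable per group, and on 3 mm as the SD before age is added. If more of the 50 per group are evaluable, planned power is higher (0.91 at 50) and there is less left to gain. The required 37 per group stands.

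**What to change.** Before any unblinding, amend the primary model to treatment, center, lesion-to-pulp distance and age, with age as a continuous linear covariate. Use the same model in the full analysis set.

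If contralateral 2PD is to be used, confine it to a supportive analysis, with a stated rule for which value applies when several nerves are injured or both hands are affected.

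Cost: one line in the analysis section and one error degree of freedom (69 to 68 at 37 per group). No new data and no change to the sample size.
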